### Data Analysis Plan

All analyses for the T-CHARM study will be conducted using the latest version of Stata (StataCorp). Data entry and cleaning will be performed by trained personnel using a double-entry verification system to ensure data integrity.

#### Missing Data Handling

For missing outcome data at follow-ups, the last observation carried forward method will be applied. Sensitivity analyses will be conducted to evaluate the robustness of findings under alternative missing data assumptions, including complete case analysis and multiple imputations if appropriate.

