**Conclusions:**

The strength of the T-CHARM study’s approach is its detailed occupational and environmental factors and longitudinal health data from the corporate clinic or the district health center, as well as links to cancer and mortality registries and self-reported health. The current phase of the study focuses on baseline data collection for long-term follow-up. The cohort will be monitored for up to 20 years, depending on sustained funding. T-CHARM offers a robust framework for understanding the chronic health effects of occupational TDE.

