### Data Collection Method

#### Overview

Baseline data for the T-CHARM study were collected through direct, face-to-face interviews conducted by researchers, with support from physicians and trained surveyors. Data collection took place at the tobacco factory and associated workplaces. A structured questionnaire was administered, comprising closed-ended questions across multiple domains, including sociodemographic information, duration of employment, medical history, smoking status, menstrual history [11], hydration status, ergonomic concerns [12], physical activity levels [13], sleep quality [14], anxiety potential [15], and tobacco exposure assessment.

In addition to the questionnaire, a series of clinical and physiological examinations were performed to evaluate the general health status of participants. These included vital signs assessment [16], BMI calculation, ergonomic observation [17], pulmonary function testing using a portable spirometer (Contec SP10, Contec Medical System Co, Qinhuangdao, Hebei, China) [18], and venous blood sampling (3 mL) for serum analysis, including complete blood count, blood glucose, lipid profile, liver function, and renal function tests. Furthermore, a random urine sample was collected in a sterile container to analyze urine profile and cotinine levels, adjusted for creatinine concentration, using an enzyme-linked immunosorbent assay. To monitor longitudinal changes in health parameters, the same data collection protocol will be repeated every 5 years over 20 years (Figure 2).

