#### Bioindicator Sampling

Tobacco leaves are also collected to study the accumulation of airborne pollutants, particularly radionuclides and heavy metals, as bioindicators of environmental exposure.

Figure 3 illustrates the recruitment process for the T-CHARM study. The exposed group consisted of a total population of 2333 women who work in tobacco processing, of whom 1816 met the eligibility criteria following screening. From this eligible pool, a target sample of 200 participants was estimated and recruited. To ensure comparability, the unexposed group—women who were nonsmokers and residents of nearby communities—was also designed to include 200 participants, matched by key demographic and environmental factors. The total cohort size for follow-up is projected to reach 400 participants, with data collection encompassing baseline and longitudinal health metrics. All collected data are subjected to analysis using appropriate statistical tools, as outlined in the study’s analysis plan.

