#### Group Comparisons

Comparative analyses between the exposed and unexposed groups will be performed for respondent characteristics, health examination results, medical history, lung function, and blood and urine parameters. Statistical tests will include Student *t* test for continuous (ratio) variables and Pearson *χ*^2^ test or Fisher exact test for categorical variables, and *P* values <.05 will be considered statistically significant.

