### Strengths and Limitations

The goal is to understand how TDE affects health over a person’s lifetime. At enrollment, the T-CHARM study collects demographic and occupational data (eg, current address, job role); lifestyle factors (eg, smoking status, dietary habits); biomarkers of exposure, including urine cotinine and other relevant indicators; and general health assessments, covering cardiovascular, respiratory, hepatic, renal, and metabolic parameters. Follow-up assessments will update exposure metrics and health status periodically, enabling dynamic tracking of disease progression and risk factors [39].

T-CHARM’s major asset is its multisource medical data integration, which includes clinical records from corporate clinics and district health centers; national health insurance data, offering continuity and completeness; and direct input from general practitioners affiliated with the research team, allowing for nuanced clinical insights beyond standard registry linkages. This approach mitigates common limitations in cohort studies, such as recall bias and loss to follow-up from self-reported questionnaires.

While traditional epidemiological studies focus on cancer, respiratory, and cardiovascular diseases, T-CHARM broadens the scope to include neurological disorders, degenerative diseases, and chronic morbidity patterns linked to environmental and occupational exposures. The longitudinal nature of general practitioner data enables detailed tracking of disease onset, progression, and comorbidities—offering a more comprehensive understanding of health trajectories in exposed populations.

Existing biases or weaknesses have been minimized, but as a cohort study, there are some limitations. The limitations include changes in characteristics of participants over time, loss to follow-up, and confounding variables that complicate data analysis due to a lack of randomization. Potential respondents are also sometimes difficult to recruit due to the invasive nature of blood collection. Additionally, biases can arise from knowledge of exposure status, participant dropout, changes in behavior due to participation, and data quality issues in retrospective studies.

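### Last observation carried forward is the main rule for missing outcomes in a cohort measured every 5 years for up to 20 years; it biases the exposure effect, in a direction that depends on loss in each group

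*Protocol article*

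**What the plan says.** Under Missing Data Handling, the protocol article fixes the rule for follow-up data: "For missing outcome data at follow-ups, the last observation carried forward method will be applied". The next sentence commits to sensitivity analyses under other assumptions, "including complete case analysis and multiple imputations if appropriate". The word primary is not used, but setting these methods apart as sensitivity analyses makes carrying forward the main rule. No reason is given for choosing it.

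The Overview of the data collection method sets the schedule, "the same data collection protocol will be repeated every 5 years over 20 years", and the purpose, "To monitor longitudinal changes in health parameters". The abstract makes the horizon conditional: "The cohort will be monitored for up to 20 years, depending on sustained funding". Entry age is 18 to 55 years (Inclusion Criteria), and the first 60 exposed women had a mean age of 40 (Results).

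Strengths and Limitations expects attrition: "The limitations include changes in characteristics of participants over time, loss to follow-up". It gives no rate for either group.

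**The concern.** Carrying forward assumes that nothing changes after a woman is last seen. That is hard to defend for lung function, glucose, lipids and renal function over decades. A woman enrolled at 40 and never seen again would enter the year-20 comparison with her value from age 40 standing for age 60.

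The damage depends on who is lost. The groups come from different employers, eligibility requires active employment, and baseline data were collected at the factory and associated workplaces. Leaving a job may therefore affect contact differently in the two groups. If so, they are frozen at different average ages, and that difference alone becomes part of the estimated exposure effect. The rule applies to every follow-up outcome, and so to the long-term comparison for which the cohort was set up.

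**Working it through.** **Reproducing a stated figure.** There is none. The document gives no effect size, standard deviation, power or loss rate.

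**Inputs from the document.** Waves at years 0, 5, 10, 15 and 20. 200 women per group: "The total cohort size for follow-up is projected to reach 400 participants". Significance: "values <.05 will be considered statistically significant", with sidedness not stated and two-sided assumed here.

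**Assumed inputs.** Linear decline in a lung-function measure of 40 mL/year (exposed) and 30 mL/year (unexposed). A constant fraction d lost at each wave, without return, unrelated to outcome within group. Loss of 5% to 30% per wave.

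**Age of a carried value at year 20.** Last seen at year 0, 5, 10 or 15, it is 20, 15, 10 or 5 years old.

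**Expected time last seen.** T(d) = 5 × [(1-d) + (1-d)² + (1-d)³ + (1-d)⁴].

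- d = 0.10: 5 × (0.9 + 0.81 + 0.729 + 0.6561) = 15.48 years
- d = 0.15: 5 × (0.85 + 0.7225 + 0.6141 + 0.5220) = 13.54 years
- d = 0.20: 5 × (0.8 + 0.64 + 0.512 + 0.4096) = 11.81 years
- d = 0.30: 5 × (0.7 + 0.49 + 0.343 + 0.2401) = 8.87 years

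The last term of each bracket is the fraction still seen at year 20: 66%, 52%, 41% and 24%.

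**Estimated difference in change, exposed minus unexposed.** Carrying forward gives -40 × T(d₁) + 30 × T(d₀), where d₁ is exposed loss and d₀ unexposed loss. The true value is 20 × (-40 + 30) = -200 mL.

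| Loss per wave, exposed / unexposed | Calculation | Result (mL) |
|---|---|---|
| 15% / 15% | -541.7 + 406.3 | -135 |
| 20% / 10% | -472.3 + 464.3 | -8 |
| 30% / 10% | -354.6 + 464.3 | +110 (reversed) |
| 10% / 20% | -619.0 + 354.2 | -265 (inflated) |
| 10% / 30% | -619.0 + 266.0 | -353 (inflated) |

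**Equal loss.** The share of the true difference kept is T(d)/20: 0.88 at 5% per wave, 0.77 at 10%, 0.68 at 15%, 0.59 at 20% and 0.44 at 30%.

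**Reversal.** With these slopes and 10% unexposed loss, exposed loss must exceed about 21% per wave.

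**No true difference (30 mL/year in both groups).** The result is 30 × [T(d₀) - T(d₁)]. At 20% / 10% it is 30 × (15.48 - 11.81) = +110 mL, falsely favouring the exposed group. At 10% / 20% it is -110 mL. Under equal loss it is 0.

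**Simulation check.** 2000 runs, 200 per group, assumed slope SD 15 mL/year and residual SD 100 mL. Carrying forward gave -8.2 mL at 20% / 10% and -265.8 mL at 10% / 20%, and +110.0 mL at 20% / 10% with no true difference. All agree with the formula. Women actually seen at year 20 gave -198 to -201 mL in every pattern with a true effect.

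**Mixed model.** On 60 simulated data sets with 20% / 10% loss and residual SD 120 mL, it gave -191 mL (Monte Carlo SE 5).

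**The case against.** **Sensitivity analyses are already planned.** This is a fair point. The plan commits to them, and the qualifier about appropriateness most naturally attaches to multiple imputation only, so the complete-case analysis is firm. If loss is unrelated to outcome within group, it would recover about -200 mL and expose the discrepancy. It would still leave the carried-forward estimate as the main result.

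**Other data sources.** Clinic, insurance and registry records may reduce loss. The missing-data rule does not use them to replace missing values, and nothing says they contain the study's own spirometry or cotinine measurements.

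**Direction.** A reader might infer that the rule necessarily hides harm. The documents do not support that. They give no loss rates, and contact through the corporate clinic could equally favour retention of exposed women, in which case the effect is inflated. A constant group difference already present at baseline would not shrink at all under equal loss.

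**Standard errors.** A reader might also infer that they come out too small. In the setting simulated they do not: with equal 20% loss and no effect, the t test rejected in about 5% of runs. The fault is bias.

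**False-positive rates.** With no true effect and 20% / 10% loss, a t test on change from baseline rejected in 88% of runs. However, Group Comparisons names a t test without mentioning change scores. On year-20 levels, with an assumed between-person SD of 300 to 500 mL and residual SD 120 mL, rejection was 67% to 42%. At 15% / 12% loss it was 13% on change and 9% on levels. No single rate should be quoted as the plan's error rate.

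**Deaths.** The text does not say that values are carried past death, and mortality linkage is planned. It does not exclude it either.

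**Timing.** Baseline results are unaffected, and follow-up depends on funding.

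**Conclusion.** The concern holds as a defect of the stated rule. Values frozen for 5 to 20 years follow directly from the schedule, and assuming no change after the last visit conflicts with the aim of measuring longitudinal change.

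The direction and size of the bias cannot be fixed from the document. For an effect that builds up over time, equal loss biases it towards zero: 68% is kept at 15% loss per wave. Unequal loss can nearly remove it (-8 mL), reverse it (+110 mL at 30% / 10%) or inflate it (-265 mL) against a true -200 mL. It can also produce a spurious 110 mL difference in either direction where there is none. These figures rest on assumed linear slopes and on constant loss unrelated to outcome within group. Confidence is high that the rule is unsuitable, and low about which way it would err in this cohort.

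**What to change.** Rewrite Missing Data Handling as follows:

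- **Continuous outcomes.** Make the main follow-up analysis a likelihood-based mixed model on all observed waves, with group, time and their interaction, adjusted for age and other baseline confounders already collected. Multiple imputation under missing at random is an acceptable alternative.
- **Binary outcomes.** Use generalised mixed models or multiple imputation.
- **Deaths.** State that no values are imputed after death.
- **Sensitivity.** Add a missing-not-at-random analysis. The mixed model was checked here only with loss unrelated to outcome within group, so that check says nothing about women who leave because their health is failing.
- **Carrying forward.** Drop it, or keep it only as a labelled sensitivity analysis.

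The cost is a change of wording and slightly more analysis work in Stata, which is already the planned software. Data collection began in July 2024 and the first follow-up wave is due 5 years after baseline, so no follow-up data are affected. The price is reliance on missing at random, which is why the further sensitivity analysis is needed.

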#### Outlier Management

Outliers in biomarker measurements will be identified using the IQR method. Outliers will be retained unless a confirmed analytic error or sample contamination is identified. Results will be assessed with and without outliers to determine their influence on statistical outcomes.

#### Group Comparisons

Comparative analyses between the exposed and unexposed groups will be performed for respondent characteristics, health examination results, medical history, lung function, and blood and urine parameters. Statistical tests will include Student *t* test for continuous (ratio) variables and Pearson *χ*^2^ test or Fisher exact test for categorical variables, and *P* values <.05 will be considered statistically significant.

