#### Exploratory Subgroup Analyses

To minimize bias and explore potential effect modifiers, subgroup analyses may be stratified by BMI, age, and length of employment. These stratified analyses will help identify differential health impacts and refine risk estimates across population subgroups.

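### Continuous lung function has only an unadjusted t test, with no age- and height-standardised scale or covariate; standardising or adjusting would be a free improvement

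*Protocol article*

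**What the plan says.** All references are to the protocol article.

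- **Overview (Data Collection Method).** The baseline examination includes "pulmonary function testing using a portable spirometer" and a BMI calculation. The article never mentions height, but BMI cannot be calculated without it. The same data collection is to be repeated every 5 years over 20 years.
- **Group Comparisons.** Exposed and unexposed women are compared on several domains, including "medical history, lung function, and blood and urine parameters". The section continues: "Statistical tests will include Student *t* test for continuous (ratio) variables", with Pearson chi-squared or Fisher exact tests for categorical variables and a 5% significance level. It names no covariate.
- **Exploratory Subgroup Analyses.** The only further step is that "subgroup analyses may be stratified by BMI, age, and length of employment".
- **Bioindicator Sampling (the paragraph on recruitment).** The unexposed group "was also designed to include 200 participants, matched by key demographic and environmental factors". The factors are not listed. The total is 200 per group, 400 in all.
- **Strengths and Limitations.** Confounding from the lack of randomisation is acknowledged.

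No section names the spirometric index (FEV1, FVC or their ratio), the scale (litres, percent predicted or z-score) or a reference equation.

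**The concern.** Spirometric volumes rise with height and fall with adult age, whatever the exposure. A t test on litres leaves both sources of variation in the residual. In a comparison that is not randomised, it also attributes any systematic difference in stature or age to working in tobacco processing.

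BMI strata do not solve this, because two women with the same BMI can differ widely in height. Age strata are optional and exploratory, and do not enter the stated test.

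Lung function is a named health outcome and plausibly the one closest to inhaled dust. A real effect could be missed for want of precision, and a difference in body size could mimic or mask one. The scale would also carry forward to every later wave.

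**Working it through.** The article gives no SD, effect size or power figure for lung function, so there is no stated figure to reproduce. What follows illustrates the raw-volume case only.

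**Inputs from the article:** 200 women per group planned; significance level 5% (two-sided assumed).

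**Inputs assumed, not from the article:** FEV1 SD 450 mL; 20-35 mL per cm of height, height SD 5.5 cm; 20-30 mL per year of age, age SD 8 years; age and height uncorrelated. Central slopes are 30 mL/cm and 25 mL/year.

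**1. Variance explained.** R² = [(age slope × 8)² + (height slope × 5.5)²] / 450², with 450² = 202,500.

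| Case | Age part | Height part | R² |
|---|---|---|---|
| Low | 160² / 202,500 = 12.6% | 110² / 202,500 = 6.0% | 19% |
| Central | 200² / 202,500 = 19.8% | 165² / 202,500 = 13.4% | 33% |
| High | 240² / 202,500 = 28.4% | 192.5² / 202,500 = 18.3% | 47% |

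Age supplies the larger share: about 20 of the 33 points in the central case.

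**2. What adjustment is worth.** The sample-size equivalent is 1/(1 − R²), if the groups are balanced on age and height.

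- Age and height together: 1/0.814 = 1.23, 1/0.668 = 1.50 and 1/0.533 = 1.88, that is, 23%, 50% and 88% more women.
- Height alone: 1/0.940 = 1.06 to 1/0.817 = 1.22, that is, 6%-22% more women.

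The smallest difference detectable with 80% power by the plain t test at 200 per group is (1.96 + 0.84) × √(2/200) = 0.28 SD. With adjustment, power for that difference is Φ(2.8/√(1 − R²) − 1.96) = 87%, 93% and 97% in the three cases.

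**3. Bias from a systematic height difference.** A true 2 cm difference in mean height shifts mean FEV1 by 2 × 20 = 40 mL to 2 × 35 = 70 mL, or 0.09-0.16 SD. The standard error of the group difference is √(2/200) = 0.10 SD. At 30 mL/cm with no dust effect:

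- 2 cm: 60/450 = 0.133 SD; the t test is significant 26.5% of the time (noncentral t).
- 3 cm: 90/450 = 0.20 SD; significant 51% of the time.

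Across 20-35 mL/cm, the rates are 14%-34% at 2 cm and 26%-64% at 3 cm. If the height-FEV1 correlation is instead taken as 0.3-0.6 (the slopes above imply 110/450 = 0.24 to 192.5/450 = 0.43), a normal approximation gives 19%-59% and 37%-91%.

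**4. Could chance produce such gaps?** The standard error of the difference in mean height is 5.5 × √(2/200) = 0.55 cm, so 95% of chance gaps lie within about 1.1 cm. Gaps of 2 and 3 cm are 3.6 and 5.5 standard errors and would need a true difference between the source populations.

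**The case against.** **The scale is unstated.** A condensed article may leave the spirometric index and reference equation to a fuller document. Percent predicted or z-scores already contain age and height, and FEV1/FVC depends on height far less. The article also does not tie lung function to the t test explicitly: tests are said to include it, and spirometry graded normal or abnormal would go to a chi-squared test. This stands, and it makes the harm conditional. It does not remove the point, because the only test stated for a continuous lung measure is unadjusted and a better one costs nothing.

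**Tempting stronger readings.** A reader might infer that any height difference will be read as dust damage. The documents do not support that. Small gaps matter little, and taller exposed women would mask an effect rather than create one. Chance gaps leave the long-run error rate at 5%, because height variation is already in the outcome SD. Nor do the documents show a systematic gap: both groups are women from the same district, and matching is planned. The matching factors are unlisted, however, and height is not ordinarily a demographic factor, so balance is not assured either.

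**Height alone is modest.** This stands: about 6%-18% of variance. The larger gain needs age as well, which appears only as an optional stratification factor.

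**Repeat waves.** Adult height is nearly constant, so within-woman change largely removes it. That is fair, but the stated test compares groups, and the baseline comparison has no such protection.

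**Conclusion.** The point holds as a free improvement, not as a demonstrated bias. The plan's only stated test for continuous lung function, in a non-randomised comparison, uses neither an age- and height-standardised scale nor those covariates. If raw volumes are compared, the precision loss arises even when the groups are balanced, and equals 23%-88% more women (central 50%) under the assumed slopes and SDs. Bias arises only from a systematic age or height difference, whose existence and direction the article does not show. If percent predicted or z-scores are already intended, little changes beyond saying so.

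**What to change.** In Group Comparisons, replace the plain t test for spirometry with one of the following, chosen before the groups are compared:

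- age- and height-standardised z-scores from one named reference equation, the same for both groups and all waves; or
- a linear model on litres with group, age and height.

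Name the spirometric indices in the same sentence, and state that height is recorded as a variable in its own right and not only used to calculate BMI.

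The cost is one sentence and no new measurement. It is best settled before the baseline results are analysed, since the same scale should serve the 5-yearly waves.

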## Results

The T-CHARM study was officially funded in the year 2024, with data collection commencing in July 2024. As of August 2025, the study has successfully enrolled 60 participants in each group—women who are nonsmokers and work in tobacco processing (exposed group) and women who are nonsmokers and community members (unexposed group). Recruitment for an additional 80 participants is currently underway, alongside laboratory analyses for the second phase of baseline data collection. These analyses include biomarker profiling, clinical assessments, socioeconomic status, and environmental exposure measurements. The cohort baseline results are expected to be published by the end of 2025, marking a key milestone in the study’s longitudinal design and setting the foundation for future follow-up waves.

In general, among the 60 women recruited for the exposed group, most of them were obese (n=28, 46.7%) and overweight (n=11, 18.3%), 76.7% (n=46) were of Madurese ethnicity, 53.3% (n=32) had education in elementary school, and 45.0% (n=27) were educated until middle and high school. Their mean age was 40 (range 21-52) years. Compared to the other work in that area, tobacco workers are paid well, with 76.7% (n=46) having an income as high as 875,000 IDR (US $52.50). Another key finding is that all the study participants are nonsmokers but exposed to tobacco dust occupationally, and 57.1% (n=60) reported being passive smokers. Health questionnaire answers showed that 60 people complained of eye problems, 28 had dermatological issues, 5 had respiratory diseases, 11 had cardiovascular disease, 60 had neurological problems, and 37 had reproductive issues.

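### The unexposed group is said to be matched, but the tests named for the group comparison ignore the matching, so they are conservative wherever the matching factors predict the outcome

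*Protocol article*

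**What the plan says.** **Design.** The text describing the recruitment flowchart (Protocol article, under Bioindicator Sampling) gives the exposed group as "a target sample of 200 participants was estimated and recruited". The unexposed group "was also designed to include 200 participants, matched by key demographic and environmental factors". The groups are equal in size, and "The total cohort size for follow-up is projected to reach 400 participants". The matching factors are not listed, and the text does not say whether women were paired individually or the groups were balanced by frequency. The Unexposed Group section describes these women only by smoking status, non-tobacco work and district.

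**Analysis.** Group Comparisons covers respondent characteristics, health examination results, medical history, lung function, and blood and urine parameters. It states: "Statistical tests will include Student *t* test for continuous (ratio) variables and Pearson" chi-square "test or Fisher exact test for categorical variables", and P "values <.05 will be considered statistically significant". Elsewhere in the Data Analysis Plan there is no paired or conditional method and no adjustment for matching factors. Exploratory Subgroup Analyses allows optional strata by BMI, age and length of employment, but does not link them to the matching.

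**The concern.** The stated analysis does not fit the stated design. Pearson chi-square and Fisher exact tests are for independent groups, and so is the Student t test unless its paired form is specified, which it is not here.

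Matching on something that predicts the outcome (age, for lung function or lipids, would be an example) makes the two groups more alike on that outcome than two independent samples would be. The mean difference then varies less than the two-sample formula says. Intervals come out too wide and P values too large. This concerns precision only: the estimated mean difference is unchanged, and the issue would remain even if matching had removed all confounding.

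In a study of occupational harm, a conservative test errs toward reporting no difference. Baseline results are expected by the end of 2025, so these tests are close to being applied.

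**Working it through.** **Inputs from the article.** 200 women per group, 400 in total (200 + 200); significance at P < .05, taken here as two-sided. The article gives no effect size, SD or power for the 200, so there is no planned power figure to reproduce.

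**Assumptions.** Continuous outcome, SD = 1, normal approximation. rho is the correlation induced by matching: between pair members, or, for frequency matching, roughly the share of outcome variance that the matching factors explain. The article gives no value, so the range is 0 to 0.5.

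**Formulas.**
- SE used by the independent-groups test: SE_ind = sqrt(2/n) = sqrt(2/200) = 0.100
- True SE under matching: SE_true = sqrt(2(1 − rho)/n)
- Reference difference, 80% power with independent groups: d = (1.960 + 0.842) × 0.100 = 0.280 SD
- Size of the nominal 5% test: 2 × [1 − Φ(1.96 × SE_ind / SE_true)]
- Actual power of the independent-groups test: Φ((d − 1.96 × SE_ind) / SE_true)
- Power of a test that uses the matching: Φ(d / SE_true − 1.96)

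**Example, rho = 0.3.** SE_true = 0.100 × sqrt(0.7) = 0.0837.
- Size: 2 × [1 − Φ(0.196/0.0837)] = 2 × [1 − Φ(2.34)] = 0.019
- Independent-groups power: Φ((0.280 − 0.196)/0.0837) = Φ(1.01) = 84.3%
- Matching-aware power: Φ(0.280/0.0837 − 1.96) = Φ(1.39) = 91.8%

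**Results.**

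| rho | Interval too wide by | True size | Power, independent test | Power, using matching | Points lost | Difference detectable at 80% using matching |
|---|---|---|---|---|---|---|
| 0 | 0% | 0.050 | 80.0% | 80.0% | 0 | 0.280 SD |
| 0.1 | 5% | 0.039 | 81.3% | 84.0% | 2.7 | 0.266 SD |
| 0.2 | 12% | 0.028 | 82.7% | 88.0% | 5.3 | 0.251 SD |
| 0.3 | 20% | 0.019 | 84.3% | 91.8% | 7.5 | 0.234 SD |
| 0.5 | 41% | 0.006 | 88.3% | 97.7% | 9.4 | 0.198 SD |

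**Simulation check.** With 20,000 runs of independent and paired t tests at n = 200 and a 0.28 SD difference, power was 83.4% against 91.1% at rho 0.3, and 88.6% against 97.8% at rho 0.5. The independent test's size was 0.021 and 0.006. This agrees with the table.

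**Present enrolment.** The article reports that "the study has successfully enrolled 60 participants in each group". At 60 per group the difference detectable with 80% power is 0.51 SD with independent groups, and 0.43 SD using the matching at rho 0.3.

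The table is for continuous outcomes. For binary outcomes the direction is the same, but these figures do not carry over exactly.

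**The case against.** The strongest objection is that the matching may amount to little. The inclusion criteria restrict both groups to nonsmoking women aged 18 to 55 with the same working hours, and both come from one district. A factor that is constant across all participants, such as sex, district or smoking status, induces no correlation. If that is all the matching means, rho is near 0 and the named tests are correctly sized. This stands, and it is why the range starts at 0. Equally, rho = 0.5 would need the matching factors to explain about half the outcome variance, which nothing in the article supports.

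A second objection is that the list of tests is introduced as inclusive rather than exhaustive, that a Student t test can be paired, and that a condensed article may leave detail to a fuller plan. The Abstract also says health effects will be evaluated in relation to urine cotinine, so the two-group tests are not the whole analysis. This narrows the point but does not remove it. The article commits to specific tests for the group comparison; the categorical ones are unambiguously for independent groups, and none is tied to the matching it describes.

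A reader might infer more: that real differences will be missed, that women were individually paired, or that the cohort falls short on power. The documents support none of these. rho is not given, pairing is not stated, and for the 0.28 SD difference the independent test's power rises with rho from 80% to 88%. The loss is only relative to a more efficient analysis.

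**Conclusion.** The point holds as a mismatch between design and analysis, with a conditional and conservative consequence. If the matching factors predict the outcome, the independent-groups standard error is too large by a factor 1/sqrt(1 − rho), the true size is below 5%, and real differences can be missed. At 200 per group and 0.28 SD the cost runs from nothing (rho 0) to about 9 points of power (rho 0.5), passing 5 points at about rho 0.2.

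Both rho and the 0.28 SD difference are assumptions, as is the two-sided test. False positives are not inflated. This is a minor point, worth correcting because the correction is cheap.

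**What to change.** In Group Comparisons:

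1. State whether matching was individual or by frequency, and list the factors.
2. Make the outcome comparison a linear or logistic regression of outcome on exposure group that includes the matching factors.
3. If women were individually paired, use instead a matched-set mixed model or paired t test for continuous outcomes, and conditional logistic regression or the McNemar test for binary outcomes.
4. Keep the t, chi-square and Fisher tests for describing the two groups.

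**Cost.** Plan wording and slightly more analysis work. No new participants or measurements are needed, provided the matching factors are recorded for both groups; the questionnaire already covers sociodemographic information. The regression spends a few degrees of freedom. With strict pairing they fall from 398 (200 + 200 − 2) to 199 (200 − 1), which is negligible at this size, and a pair that loses one member drops out of a paired test. The mixed model avoids that loss.
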